**Fig. 1 Fig1:**
[figure not shown]
CONSORT flow diagram, indicating the schedule of enrolment, interventions and assessments of the study

Individual qualitative interviews with a purposive sample of 30 individuals from each intervention cohort will be conducted (1-month post-intervention) to explore their overall perception of using mindfulness for psychological distress management. The focus will be placed on how and why they perceive mindfulness practice to influence or not influence their psychological distress and acceptance of the intervention. The qualitative findings will be used to enhance the interpretation of the quantitative findings about the effect and mediating process of mindfulness on psychological distress and to inform the application of the findings [31]. The development-evaluation-implementation process of this study follows the Medical Research Council’s framework for complex interventions [32].

### Study participants

Eligible participants will be (i) diagnosed with idiopathic, mild-to-moderate PD as indicated by the Hoehn and Yahr Scale [33] Stages I to III (presented with unilateral to bilateral symptoms, with or without postural instability), (ii) aged ≥ 18 years, and (iii) able to give written consent. Individuals will be excluded if they: (i) have been regularly practicing instructor-led mindfulness interventions once a week or more during the past 6 months, (ii) are currently participating in any other behavioural or pharmacological trial, (iii) have significant cognitive impairment as indicated by the Abbreviated Mental Test lower than 6 [34], or (iv) have other contraindication or severe comorbidity that may limit their full participation (e.g. severe hearing or vision impairment, etc.).

### Sampling and recruitment strategies

Potential participants will be recruited from (i) neurological outpatient clinics at three regional hospitals: Queen Mary Hospital (QMH), Tung Wah Hospital (TWH), and Pamela Youde Nethersole Eastern Hospital (PYNEH), and (ii) PD support groups: Hong Kong Parkinson’s Disease Foundation (HKPDF), Hong Kong Parkinson’s Disease Association (HKPDA) and Community Rehabilitation Network (CRN). To enhance sample accessibility and representativeness, recruitment and intervention sites will cover three major local districts. Combinations of recruitment strategies will be used, including electronic mailing, printed flyers within the community centres and outpatient clinics, and dissemination of newsletters among patient support groups. Health talks will be held in community centres to aid recruitment, if necessary. All promotional materials and registration will be made accessible online.

### Allocation concealment, assignment of interventions and blinding

After baseline assessment, participants will be randomly assigned into one of the three groups on a 1:1:1 basis using the method of permuted block, with random block sizes between 3, 6, and 9, and will be informed of their assigned group by an independent person not involved in the assessment. The allocation list will be computer-generated by an independent researcher and concealed from other researchers and participants until the time of assignment.

### Study intervention

#### Meditation group

The mindfulness meditation intervention will be adapted from the structured eight-week mindfulness-based stress reduction (MBSR) program conceptualised by Jon Kabat-Zin [35] except the yoga component will be replaced by mindful movements with minimal physical exertion, and guided by our previous experiences of teaching mindfulness among local PD patients [36–38]. Previous PD literature reported that frequent and lengthy mind-body interventions (more than 3 times per week, with a total time > 180 min per week) were associated with reduced effectiveness owing to the decreased adherence and increased physical intolerance experienced by PD patients, and suggested a moderate dose of about 120 min per week as a feasible and practical mind-body practice for PD patients [27]. Hence, compared to the standard MBSR program (8 weekly 2.5-hour sessions, one all-day session between sessions 6 and 7, and daily 45-min homework), the tested meditation intervention will be modified to 8 weekly 90-min sessions, with 12 contact hours in total. Participants will be encouraged to perform 20-min home-based practice two times a week. The intervention will be delivered in neutral terminology free from any religious affiliation by a qualified MBSR instructor, and in a face-to-face group format of about 15–20 participants at local community centres.

The theme of each session reflects one of the 8 attitudes of mindfulness: non-judging, patience, beginner’s mind, trust, non-striving, acceptance, letting go, and generosity. The content and outline of the intervention are shown in Table 1, which has been adapted and modified from our previously tested meditation protocol for PD [38]. The weekly session consisted of standardized core elements of mindfulness practices: (i) guided meditation techniques (such as mindful breathing, body scan, etc.) focusing one’s attention on the breath, bodily sensations and non-judgmental awareness, and (ii) practicing being fully aware during everyday activities by using the breath as an anchor for the attention. If the instructor notices that participants start falling asleep (as indicated by head bobbing or snoring), various strategies will be used such as increasing voice volume, altering intonation, giving verbal cues, or changing meditation sequence, for example, chanting a simple mantra with participants. Paper handouts regarding the mindfulness techniques will be given to facilitate the learning and self-practice.

**T﻿able 1 Tab1:** Theme and outline of the yoga and meditation programs

	Week 1		Week 2		Week 3		Week 4	
Program	Yoga	Meditation	Yoga	Meditation	Yoga	Meditation	Yoga	Meditation
Theme	Beginner’s mind: Introducing mindfulness		Patience: Allowing time for purifying mind, body and spirit		Non-judging: cultivating awareness towards inner and outer experiences		Acceptance: Embracing, exploring and expanding own limitations	
Outline	Warm up (Standing) 1. Mountain pose with balance shifting (centered, left, right, forward, heels) 2. Alternating between mountain and chair poses with synchronized breathing and arms movement Yoga sequence with mindful breathing 1. Crocodile pose 2. Sphinx pose 3. Cobra pose 4. Child pose Yoga nidra meditation	Guided body scan meditation in supine position Discussion: observation of daily stressful events	Warm up (as week 1) Yoga sequence (Standing) 1. Mountain pose 2. Side bend 3. Revolted forward bend 4. Lotus mudra 5. Cow face pose with forward bend 6. Lion’s breath Thoracic breathing Diaphragmatic breathing Mindful breathing Mindful eating	Guided body scan meditation in seated position Seated pose for meditation (On chair/ yoga block/ yoga mat) 1. Easy pose 2. Perfect pose 3. Half lotus 4. Full lotus 5. Diamond pose 6. Hero pose Mindful breathing Discussion: observation of daily pleasant events	Warm up (as week 1) Yoga sequence (Supine) 1. Mountain pose 2. Upward salute 3. Neck turning 4. Single leg raises with ankle rotation 5. Double leg raises 6. Bridge pose 7. Knees to chest pose 8. Corpse pose Santosha guided meditation in corpse pose Soham mantra meditation (seated)	Guided mindful breathing meditation in seated position Gentle mindful movement 1. Supine mountain pose 2. Supine upward salute 3. Knees to chest pose 4. Cat and cow pose 5. Balancing cat pose 6. Bridge pose 7. Supine spinal twist 8. Supine leg raises 9. Sleeping Vishnu pose 10. Front corpse pose 11. Half locust pose 12. Corpse pose Discussion: observation of daily unpleasant events	Warm up (as week 1) Yoga sequence (Standing) 1. Triangle pose 2. Warrior II pose 3. Side angle pose 4. Wide-legged forward bend Modified sun salutations 1. Mountain pose 2. Upward salute 3. Standing forward bend 4. Low lunge 5. Child pose 6. Tabletop pose 7. Knee, chest, chin pose 8. Cobra pose 9. Child pose 10. Downward-facing dog 11. Standing forward bend 12. Upward salute 13. Mountain pose Three-minute breathing space Yoga nidra meditation	Guided naming meditation in seated position Three-minute breathing space The stress-reaction cycle: respond vs react Discussion: observation of the responds towards unpleasant events

	Week 5		Week 6		Week 7		Week 8	
Program	Yoga	Meditation	Yoga	Meditation	Yoga	Meditation	Yoga	Meditation
Theme	Non-striving: Connecting to inner self without pushing		Generosity: Giving time, energy and attention to others while practicing self-compassion		Trust: Instilling confidence and loving-kindness		Letting go: Surrendering and being fully present	
Outline	Warm up (as week 1) Yoga sequence (Seated) 1. Diamond pose 2. Staff pose 3. Seated side bend 4. Cow face pose with forward bend 5. Lion’s breath 6. Camel pose 7. Rabbit pose Modified sun salutations (as week 4) Bee breath Cooling breath Om mantra meditation Yoga nidra meditation	Guided body meditation with mindful breathing in seated position Guided mindful walking Three-minute breathing space Mindful listening Discussion: observation of communication difficulties	Warm up (as week 1) Mindful walking Dyadic yoga sequence 1. Seated namaste (face-to-face) 2. Seated mountain pose with neck stretching (back-to-back) 3. Seated side bend (back-to-back) 4. Seated waist twisting (back-to-back) 5. Supported chair pose 6. Triangle pose (back-to-back) 7. Warrior II (back-to-back) 8. Tree pose (side-to-side) 9. Easy pose shoulder retraction partner Yoga nidra meditation in partner corpse pose	Guided open meditation in seated position Guided mindful walking Three-minute breathing space Mindful eating Mindful communication Discussion: cultivate awareness towards daily events and observation of body responds	Warm up (as week 1) Mindful walking Modified sun salutations (as week 4) Bee breath Alternating nostril breathing Om mantra meditation Loving kindness meditation in corpse pose	Guided loving-kindness meditation Mindful walking Three-minute breathing space Mindful living Discussion: cultivate loving-kindness towards self and the surrounding	Warm up (as week 1) Mindful walking Modified sun salutations (as week 4) Om mantra meditation Yoga nidra meditation	Open meditation in seated position Mindful breathing Mindful walking Three-minute breathing space Discussion: goal setting for continuous mindfulness practise in daily life

#### Yoga group

The mindfulness-based yoga intervention shares the same format and theme as the meditation intervention: 8 weekly 90-min sessions, with 12 contact hours in total. Participants will be encouraged to perform 20-min home-based practice two times a week. The intervention will be delivered in neutral terminology free from any religious affiliation by a qualified yoga and MBSR instructor, and in a face-to-face group format of about 15–20 participants at local community centres. The content and outline for each session are shown in Table 1, which has been adapted and modified based on our previously tested mindfulness yoga protocol for PD [37, 39]. The weekly session consisted of standardized core elements of yoga practices: (i) controlled breathing, (ii) mindfulness practice of yoga sequences (12 modified postures of sun salutations) with a focus on being aware of breath, bodily sensations and non-judgmental awareness during physical exertion, (iii) guided meditation techniques, and (iv) practicing being fully aware during everyday activities by using the breath as an anchor for the attention. Sharing of mindfulness practices experience will be facilitated by the instructor at the end of each session to consolidate learning and promote social interaction. Paper handouts regarding the mindfulness techniques will be given to facilitate the learning and self-practice.

#### Usual care group

The wait-list control group will continue with routine outpatient services (medication follow-up care with minimal health education on disease management/ drug care) and receive the tested yoga intervention [39] upon completion of the 6-month study period.

### Outcome measures

To detect the intervention effects, the following instruments will be used for outcome evaluation at baseline (Prior to randomization, T_0_), 1-week post-intervention (T_1_), and 4-month post-intervention (T_2_):

#### Primary outcomes

*Hospital Anxiety and Depression Scale (HADS)* (Chinese-Cantonese) will be used to measure anxiety and depression as primary outcomes [40]. HADS is a self-report questionnaire consisting of anxiety and depression subscales. Each subscale consists of seven items and each item is rated on a four-point scale. A high score represents a high level of psychological distress. The Cronbach alphas for the HADS-anxiety and HADS-depression subscales were 0.86 and 0.78 and construct validity is evident especially when no somatic symptom assessment is included, as such symptoms may be confused with Parkinsonian manifestations [41]. The test-retest reliability for subscales, as assessed by intraclass correlation coefficient (ICC), were 0.86 and 0.84 for the HADS-anxiety and HADS-depression [42].

#### Secondary outcomes

*Movement Disorder Society-Unified Parkinson’s Disease Rating Scale (MDS-UPDRS, Chinese)* will be used to measure PD-related motor and non-motor symptoms [43]. MDS-UPDRS consists of four parts, which examine: (i) non-motor experiences (cognitive impairment, hallucinations, depressed mood, anxious mood, apathy, and dopamine dysregulation), (ii) motor experiences of daily living, (iii) examination of motor symptoms (tremor, rigidity, bradykinesia, gait and postural instability), and (iv) motor complications (dyskinesia and motor fluctuations), respectively. Higher scores indicate greater disease severity. Cronbach’s alphas are 0.79–0.93 [44].

*Chinese Five-Facet Mindfulness Questionnaire (Short-form)* will be used to measure perceived mindfulness [45]. Using a 5-point Likert scale, this 20-item scale assess five mindfulness domains: observing, describing, acting with awareness, non-judgment of inner experience, and non-reaction to inner experience. Cronbach’s α is 0.82 [46].

*Parkinson’s Disease Questionnaire-8 (PDQ-8, Chinese)* will be used to measure PD-related HRQOL [47]. The 8-item scale yields a summary index score capturing disease-specific HRQOL regarding mobility, activities of daily living, emotional wellbeing, social support, communication, cognition, body discomfort and stigma. Higher scores indicate worse HRQOL. Cronbach’s α is 0.80 [48].

Plasma cortisol, IL-6 and TNF-α will be collected. To control for variations of cortisol levels over the circadian rhythm, all blood samples will be collected at 14:00 to 16:00, as cortisol level in this sub-period is relatively stable and highly correlated with mean 24-h cortisol level [49, 50].

The expectation on treatment credibility refers to the respondent’s expectation of the stress-reducing effect of the received intervention. A 4-item questionnaire will be used, rating: (i) reasonableness of treatment, (ii) opinion of the therapist, (iii) expectation for improvement, and (iv) likelihood to recommend the treatment to others, on a 10-point scale (higher scores indicating higher expectation) [51].

Socio-demographic and clinical data will be documented using a self-reported questionnaire, which covers participant profile (age, gender, marital status, educational level, religiosity, and financial status) and clinical data (onset time, PD staging, medication record, history of psychiatric disturbance, presence of comorbidity, history of rehabilitation service utilization). All these will be documented and considered as control variables in the data analysis.

### Data collection procedures

The researcher will contact the referred/registered potential participants by phone and screen for their eligibility. Eligible participants will be invited to a face-to-face interview at a community center. The research team will first obtain written informed consent from the participants, followed up by demographic and baseline assessments. Questionnaires in e-format will be administered using an iPad: a well-accepted data collection approach as shown by our previous PD trials [39]. A research assistant will help participants with difficulties in filling out the questionnaires. All assessments will be conducted during the ‘on’ state of medications to minimize motor fluctuations. Blood samples will be collected by qualified personnel. Neurological motor examinations will be conducted by qualified personnel with an MDS-UPDRS certificate.

Qualitative data will be collected to explore participants’ experiences. A purposive sampling of 30 participants with diversified socio-demographic characteristics from each of the intervention groups will be invited for individual interviews. This sample size complies with various guidelines which suggest that a sample of 25 participants is adequate to reach data saturation and the sample of a qualitative study should lie within 50 [52]. The pre- and post-test difference of HADS scores will be used as the pre-defined criterion, with ten participants in each range of the 0-35th, > 35-70th, and > 70th percentile. If saturation is not reached, one more case will be recruited from each percentile until no more new findings emerge. The interview guide (Table 2) will focus on exploring participants’ experience in using the mindfulness practice as a lifestyle intervention for stress management, particularly the perceived effects, how and why they work or do not work, and conditions that may influence their motivation, acceptability, and real-life practice.

**Table 2 Tab2:** Interview guide for qualitative interview

Questions	Probes
1. How do you feel about the 8-week mindfulness training? 2. How has your mood changed while you were participating in the 8-week mindfulness training? 3. How is your current mood different from the situation before you participated in the 8-week mindfulness training? 4. You have mentioned that you have improved mood after participating in the 8-week mindfulness training. What are the possible reasons leading to such changes? OR You have mentioned that your mood remains the same after participating in the mindfulness training. Why is that? What are the possible reasons? 5. Will you recommend the 8-week mindfulness training to your friends with Parkinson’s disease or with mood disturbance? Why? 6. Will you consider doing regular mindfulness practice in the future? Why?	Acceptability and tolerance Mood changes - Anxiety - Depressive symptoms - Number and duration of psychological distress - Physical fitness - Motor symptoms (tremor, rigidity, bradykinesia, gait and postural instability) - Non-motor symptoms (cognition, hallucinations, depressed mood, anxious mood, apathy, dopamine dysregulation) - Perception on psychological distress - Perceived effectiveness of mindfulness training

### Sample size estimation

To account for multiplicity, we consider 2.5% as the nominal level of significance by Bonferroni adjustment. Taking psychological distress as the primary outcome, a previous systematic review reported an effect size of 0.4 for meditation compared to cognitive behavioral therapy control [53], while our previous clinical trial reported an effect size of 0.6 for yoga compared to exercise control [39]. Taking a conservative approach, although the comparison is made to usual care, we anticipate a moderate effect size of 0.6 for the primary outcome. Using power analysis software Gpower 3.1, assuming an attrition rate of 20%, 168 participants will give a three-arm (56 each arm) RCT 80% power to detect an effect size of 0.6 at 2.5% level of significance.

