**Methods:**

We will conduct an assessor-blind three-arm randomized waitlist-controlled trial with a descriptive qualitative evaluation. Up to 168 PD patients will be recruited from community settings and out-patient clinics, and randomized to meditation, yoga, or usual care group. Meditation and yoga sessions of 90-minute are held weekly for 8 weeks. Primary outcomes include anxiety and depression. Secondary outcomes include PD-related motor and non-motor symptoms and quality-of-life; and level of mindfulness and biomarkers of stress and inflammatory responses will be measured as mediating variables. All outcome evaluations will be assessed at baseline, 8 weeks, and 24 weeks. Following the intention-to-treat principle, generalized estimating equation models and path analysis will be used to identify the treatment effects and the mediating mechanisms. A subsample of 30 participants from each intervention group will be invited for qualitative interviews.

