### Aims and hypothesis

This study aims to:

examine the effects of individual mindfulness techniques – yoga and meditation – compared to usual care, on anxiety and depression, mindfulness, PD-related motor and non-motor symptoms, HRQOL and biomarkers of stress and inflammatory responses of PD patients over the 6-month study period;investigate whether biomarkers and level of mindfulness function as mediating variables in the effects that the mindfulness practices have on anxiety and depression, respectively; and.explore the experiences of PD patients in practising individual mindfulness techniques, and conditions that may influence their motivation, acceptability, and real-life practice.

The research hypotheses to be tested are:

PD patients who receive mindfulness interventions will report greater positive changes in anxiety and depression, mindfulness, PD-related motor and non-motor symptoms, HRQOL and biomarkers of stress and inflammatory responses on the completion of the intervention and at 4-month follow up, compared to the usual care group.The effects of mindfulness practices on anxiety and depression are meditated by a reduced level of physiological markers of stress and improved level of mindfulness demonstrated at post-test assessment.

The exploratory research question is:

3.What are the participants’ experiences in using yoga and meditation as lifestyle intervention for psychological distress management, particularly the perceived effects, how and why mindfulness works or does not work, and conditions which may influence their motivation, acceptability, and real-life practice?

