## Methods

### Study design and setting

This is a multi-centre, assessor-blinded, 3-arm randomised waitlist-controlled trial with sequential mixed-method design to evaluate the effect and acceptability of 8-week programs using individual mindfulness techniques (yoga alone and meditation alone), compared to wait-list usual care control. Figure 1 shows the CONSORT flow diagram. Repeated outcome measures will be assessed at three time points across the 6-month study period to quantitatively evaluate the immediate and sustained effects of each mindfulness technique on anxiety and depression and other physio-psycho-spiritual outcomes in PD patients, compared with the usual care control group. Assessment time points are: baseline (Prior to randomization, T_0_), 8 weeks (T_1_: 1-week post-intervention), and 24 weeks (T_2_: 4-month post-intervention).

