### Data analysis

Descriptive statistics will be used to summarize the socio-demographic characteristics and clinical data (as listed above) of all subjects at all time points. Generalized estimating equations (GEE) with unstructured working covariance matrix at the individual level with repeated measurements will be performed to compare all outcomes [1–5] between groups (i.e., time effect, group effect, group*time effect). An intention-to-treat principle will be adopted. Multiple imputations will be used to account for missing data, and reporting will follow the guideline published in *BMJ* [54]. Sensitivity analysis will be performed to compare the results between complete and non-complete cases. All demographic and clinical variables (e.g. age, gender, religiosity, expectation on treatment credibility, etc.) will be accounted for in the analysis. Both crude and adjusted GEE model analyses will be performed. All statistical tests will be two-tailed and statistical significance will be set at 0.025. IBM SPSS 25.0 will be used.

Path analysis will be used to examine the mediating role of biomarkers and level of mindfulness on the effect of mindfulness training on psychological distress. Based on the hypothesized mediation model (Fig. 2), a baseline path model will be first built, then a path model with the same structure for T1 will be added and linked by intra-correlations among the same variables. The mediation effects of biomarkers and level of mindfulness on the effect of mindfulness training on psychological distress will be assessed through the significance of the corresponding products of indirect path coefficients from mindfulness training to psychological distress, respectively [55]. In view of the possibility of violation of normality assumption, a bootstrapping approach, instead of the conventional multivariate delta method, will be used to estimate the standard errors and the confidence intervals of the product terms (mediation effects) [56]. The path analyses and the bootstrapping will be performed using IBM SPSS 25.0.

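### The 2.5% Bonferroni level covers two tests, but the protocol sets up at least four primary comparisons, so family-wise error at one visit is about 7–9%, not 5%

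*Protocol article*

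**What the plan says.** Sample size estimation in the protocol article fixes both the method and the level: "To account for multiplicity, we consider 2.5% as the nominal level of significance by Bonferroni adjustment". It does not say which tests the adjustment covers. It continues with one outcome: "Taking psychological distress as the primary outcome".

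Other sections describe a larger family:

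- **Outcomes.** The abstract says "Primary outcomes include anxiety and depression". Under Primary outcomes, the two-subscale HADS "will be used to measure anxiety and depression as primary outcomes".
- **Arms.** Study design and setting describes "individual mindfulness techniques (yoga alone and meditation alone), compared to wait-list usual care control", so there are two comparisons with the same control.
- **Visits.** The first hypothesis under Aims and hypothesis expects benefit "on the completion of the intervention and at 4-month follow up, compared to the usual care group". No primary visit is named.
- **Level.** Data analysis states "All statistical tests will be two-tailed and statistical significance will be set at 0.025". It compares all outcomes by GEE "between groups (i.e., time effect, group effect, group*time effect") and makes none of these terms the primary test.

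**The concern.** The article does not leave multiplicity open. It claims to have dealt with it, names Bonferroni and gives a number, and that number fits two tests. Two active arms and two primary outcomes make four comparisons with usual care at any one visit. The divisor of two works only if one of those dimensions is dropped, and the singular outcome in the sample-size paragraph does exactly that, against the abstract and the outcome section.

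At stake is what a lone positive result means. If one of the four comparisons fell below 0.025, it could be reported as a primary finding with multiplicity controlled at 5%, when the actual control is weaker. The Discussion intends the results to inform treatment options and wider implementation.

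**Working it through.** **Inputs from the protocol article**

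- Level per test: 0.025, two-sided (Sample size estimation; Data analysis).
- Active arms compared with usual care: 2 (Study design and setting).
- Primary outcomes: 2 (abstract; Primary outcomes).
- Visits in the first hypothesis: 2, T1 and T2 (Aims and hypothesis).
- Allocation 1:1:1. With equal arms and a shared control, the two arm contrasts correlate at 0.5.

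**Assumptions, not in the article**

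- Overall target of 5%.
- Correlation between the anxiety and depression contrasts: varied from 0 to 0.8.
- Correlation between the T1 and T2 contrasts: 0.5 to 0.7 for the main range.
- All null hypotheses true; test statistics multivariate normal.

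**Step 1. Reproduce the stated level.** 0.05/2 = 0.025. The stated figure is Bonferroni for two tests.

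**Step 2. Count the comparisons.** One visit: 2 arms × 2 outcomes = 4. Both visits: 4 × 2 = 8.

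**Step 3. Bounds and independent-test values.** The upper bound is k × 0.025. If the tests were independent, the error would be 1 − (1 − 0.025)^k.

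| Tests k | Upper bound | If independent |
|---|---|---|
| 2 | 5% | 4.9% |
| 4 | 10% | 9.6% |
| 8 | 20% | 18.3% |

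**Step 4. Allow for correlation.** Simulation with 1,000,000 draws and a critical value of 2.241 (two-sided 0.025).

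- Two arms, one outcome, one visit: 4.6%. The level is adequate here.
- Two arms, two outcomes, one visit:

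| Outcome correlation | Family-wise error |
|---|---|
| 0 | 9.0% |
| 0.3 | 8.9% |
| 0.5 | 8.5% |
| 0.7 | 7.9% |
| 0.8 | 7.4% |

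- Two arms, two outcomes, both visits, if both were confirmatory:

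| Outcome correlation | Visit correlation 0.5 | Visit correlation 0.7 |
|---|---|---|
| 0.3 | 16.0% | 14.8% |
| 0.5 | 15.4% | 14.2% |
| 0.7 | 14.2% | 13.1% |

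No outcome correlation in the range tried brings four tests back to 5%.

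**Step 5. Check the remedies (one visit).** With 0.025 per arm, the bound is 2 × 0.025 = 5% for either remedy.

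- Holm within each arm: when all nulls are true, an error needs at least one of the four p-values below 0.0125. This gives 4.3% at outcome correlation 0.6.
- Fixed sequence within each arm: when all nulls are true, the error is that of the two first tests, 4.6%.

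**Step 6. Power cost of Holm's first step.** 56 per arm less 20% is 44.8, taken as 45 completers. For a two-sample t-test with effect size 0.6, power is 71.4% at two-sided 0.025 and 61.7% at two-sided 0.0125.

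**The case against.** The strongest reply is that two readings would make 2.5% correct.

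*One distress score, two arms.* The sample-size and analysis sections speak of psychological distress, and the HADS description equates a high score with distress. But the abstract and the outcome section name anxiety and depression as separate primary outcomes, so this reading contradicts them.

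*One overall between-group test per outcome.* Two primary outcomes, each with a single 4-degree-of-freedom test across arms and visits at 0.025, give a simulated family-wise error of 4.1–4.95%. This stands as arithmetic: two arms on one outcome is not the only case that fits the level. But Data analysis lists time, group and interaction effects and makes none of them primary or gating, while the first hypothesis is framed as comparison with usual care.

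A reader might also infer that eight tests are confirmatory and that an error of up to 16% is therefore established. The article does not support that. It expects effects at both visits for every outcome, biomarkers and quality of life included, and does not define a confirmatory family. The 13–16% range is conditional on both visits being confirmatory.

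Finally, a testing order may sit in an analysis plan that is not shown, so its absence is not the point. The point is the mismatch between the stated level, the stated outcomes and the stated arms.

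**Conclusion.** The point holds in this form: a level that covers two tests is applied to a design with four primary comparisons at one visit, and the sections disagree on whether there is one primary outcome or two. At one visit the family-wise error is about 7–9%, bounded by 10%, for outcome correlations of 0 to 0.8. Only if T1 and T2 are both confirmatory does it rise to about 13–16%, bounded by 20%, for outcome correlations of 0.3–0.7 and visit correlations of 0.5–0.7. These figures assume a 5% overall target and that no treatment effect exists on any primary comparison. Secondary outcomes are not counted.

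**What to change.** 1. Make the Sample size estimation paragraph agree with the abstract and the Primary outcomes section on what is primary.
2. Name one confirmatory visit and treat the other as secondary.
3. Keep two-sided 0.025 for each active arm against usual care, and within each arm control the two outcomes by one of:
   - Holm: the smaller p-value against 0.0125 and, if that succeeds, the other against 0.025. This keeps anxiety and depression as equal primaries.
   - A fixed sequence with every step ordered, chosen by the sponsor before unblinding. The article gives no basis for ranking one outcome above the other, so that choice has to be made and justified.
4. Tie the power statement to the outcome and level actually tested first.

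**Cost.** The text change is small. Under Holm the first test in each arm runs at 0.0125, so the stated power must be restated: 61.7% against 71.4% at 0.025, with 45 completers per arm, effect size 0.6 and a t-test. The stated 80% is thus not reached at two-sided 0.025 after 20% attrition either, which is a separate matter to settle when the paragraph is revised. Keeping 80% power at 0.0125 would need 64 completers per arm: 64/0.8 = 80 randomised per arm, 240 in total, against 168 planned. Under a fixed sequence the first test stays at 0.025, but every later outcome or visit in the sequence can be claimed only if the earlier tests succeed.
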